### Primary outcome

The primary outcome is a composite of development of moderate or more severe ARDS and all-cause mortality during the 30-day period following enrolment. Based on the Berlin criteria, moderate ARDS is defined by a PaO2/FiO2 > 100 mmHg and ≤ 200 mmHg, and severe ARDS a PaO2/FiO2 < 100 mmHg [26]. To determine the ARDS development, PaO2/FiO2 ratio will be monitored at least once daily. Site investigators will be reporting patient status at 30 days, irrespective of whether the patient continues hospitalized, or is discharged home. If patients are discharged alive from the hospital before day 30, the local investigator will contact the patient or relatives by phone to ensure the status of the patient on day 30 after randomization. Readmission with moderate ARDS and mortality during 30-day after randomization will be detected on the follow-up telephone call programme. Before placing a call, the patient medical record will be reviewed. Electronic health record data related to any inpatient or emergency department revisits within 30 days after discharge will be extracted.

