### Sample size

We powered the study to assess whether the intervention would reduce the incidence of ARDS. Based on available evidence, we estimate a 30% risk of ARDS in the control group [2]. We are looking for an ARDS 10% absolute reduction in the intervention group. Assuming 80% power and two-sided alpha = 0.05, 226 participants would be needed to detect the resulting reduction of ARDS from 30% in the control group to 20% in the intervention group. We adopted a sample size of 252 (126 per group) to compensate for the potential loss to follow-up of some participants.

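### The moderate and severe ARDS bands of the primary endpoint leave a PaO2/FiO2 of exactly 100 mmHg in neither band; the gap is real, its expected effect very small

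*Protocol article*

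**What the plan says.** All the relevant text is in the Primary outcome section of the protocol article.

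- The endpoint: "The primary outcome is a composite of development of moderate or more severe ARDS and all-cause mortality during the 30-day period following enrolment".
- The severity bands, attributed to the Berlin criteria: "moderate ARDS is defined by a PaO2/FiO2 > 100 mmHg and ≤ 200 mmHg, and severe ARDS a PaO2/FiO2 < 100 mmHg".
- Measurement: "To determine the ARDS development, PaO2/FiO2 ratio will be monitored at least once daily".
- After discharge, by telephone: "Readmission with moderate ARDS and mortality during 30-day after randomization will be detected on the follow-up telephone call programme".
- After discharge, from records: "Before placing a call, the patient medical record will be reviewed", and then "Electronic health record data related to any inpatient or emergency department revisits within 30 days after discharge will be extracted".

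The same section has site investigators report every patient's status at 30 days, whether still in hospital or discharged.

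**The concern.** The composite treats moderate and worse ARDS as one region of the PaO2/FiO2 scale, with 200 mmHg as its upper limit. The two bands that define the region should therefore meet at 100. They do not, because moderate starts strictly above 100 and severe lies strictly below it.

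The value is not exotic. A PaO2 of 60 mmHg on an FiO2 of 0.60, or 80 on 0.80, gives exactly 100. A derivation programmed literally from these bands would not flag such a reading, although it describes a sicker patient than a reading of 150, which does count.

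The slip is in the threshold of the primary endpoint of an open-label trial. The Discussion defends the absence of blinding partly on the ground that this endpoint is clear. A value that the rule does not classify would have to be settled by judgement, and a clear rule is meant to avoid that.

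The telephone sentence has a related looseness: it names moderate ARDS but not severe.

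**Working it through.** **Step 1. The bands.** No calculated figure in the plan bears on this point, so the check is of the inequalities themselves. A reading x counts if (x > 100 and x ≤ 200) or x < 100. Testing each integer from 50 to 201, the only value at or below 200 that fails is x = 100. The other failing value, 201, lies outside the region by design.

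**Step 2. When an event is lost.** All of these must hold:
1. the patient has a reading of exactly 100;
2. no other reading is at or below 200, although the ratio is recorded at least daily;
3. the patient is alive at day 30, since death is itself an event;
4. the bands are applied literally, against the evident sense of the composite.

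**Step 3. Size.** The documents do not say how often this happens, so the share q of events lost is an assumption, applied equally to both arms because the rule does not depend on arm. Inputs from the Sample size section:
- control risk: "we estimate a 30% risk of ARDS in the control group";
- target: "reduction of ARDS from 30% in the control group to 20% in the intervention group";
- 126 per group, two-sided alpha 0.05.

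These rates are stated for ARDS and stand in here for the composite. No loss to follow-up is assumed.

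Expected events are 126 × 0.30 = 37.8 (control) and 126 × 0.20 = 25.2 (dexamethasone), 63 in all.

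Power = Φ{[Δ − 1.96·√(2p̄(1−p̄)/n)] / √([p₀(1−p₀)+p₁(1−p₁)]/n)}, with n = 126, p₀ = 0.30(1−q), p₁ = 0.20(1−q), Δ = p₀ − p₁ and p̄ their mean.

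- q = 0: (0.1000 − 0.1069)/0.0542 = −0.128, power 44.9%.
- q = 0.05: (0.0950 − 0.1051)/0.0533 = −0.189, power 42.5%.

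| q (assumed) | Control events lost (37.8q) | Dexamethasone events lost (25.2q) | Risk difference, points (10(1−q)) | Power |
|---|---|---|---|---|
| 0 | 0 | 0 | 10.00 | 44.9% |
| 0.5% | 0.19 | 0.13 | 9.95 | 44.7% |
| 1% | 0.38 | 0.25 | 9.90 | 44.4% |
| 2% | 0.76 | 0.50 | 9.80 | 43.9% |
| 5% | 1.89 | 1.26 | 9.50 | 42.5% |

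The risk ratio stays at 0.20/0.30 = 0.67 throughout. One patient reclassified in one arm moves that arm by 1/126 = 0.79 points; this is a unit of scale, not a forecast.

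The starting power is well below the planned 80% because the stated total of 226 does not follow from its own inputs: the same method gives 294 per group, 588 in total. That is a separate matter, and the present point does not depend on it.

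**Step 4. After discharge.** Patients are in hospital when randomised, so discharge falls on or after day 0. A window of 30 days after discharge therefore always reaches at least day 30 after randomisation. The extraction covers any inpatient or emergency revisit, with no severity limit, so a readmission with severe ARDS falls inside it.

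**The case against.** The strongest reply is that the gap has no practical effect. The endpoint is binary, its wording makes clear that worse than moderate counts, and no sensible programmer would leave a reading of 100 unflagged. A patient who deteriorates to 100 will usually have another daily reading at or below 200. The article also condenses a fuller protocol, and the endpoint derivation and call scripts are not shown. Nearly all of this stands, and it is why the effect is put as very small. It does not remove the defect: the article states the bands explicitly, and as stated they do not cover the region the composite names.

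A reader might go further and infer from the telephone sentence that survivors readmitted with severe ARDS are not captured. The documents do not support that. The two sentences that follow it require record review before each call and extraction of data on any revisit, the window reaches day 30, and the endpoint itself includes severe ARDS. What remains is a sentence worded more narrowly than the endpoint.

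A reader might also quote a shift of several percentage points by placing a handful of lost patients in one arm. The documents give no count of such patients, and the rule applies to both arms alike, so losses would partly offset in the risk difference.

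**Conclusion.** The bands are wrong as written: exactly 100 mmHg is unclassified in a definition meant to cover everything at or below 200. This is a minor drafting error in the primary-endpoint threshold. It changes no alpha, power or sample-size input.

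Its consequence is confined to a patient whose sole qualifying reading is 100 and who survives to day 30, and then only if the rule is applied literally. Even a loss of 5% of events in both arms, a deliberately high assumption, costs about 2.4 points of power (44.9% to 42.5%) and 0.5 points of risk difference. That range rests on equal proportional loss in the two arms and on the planning rates of 30% and 20%. The true share is unknown and is probably at or below the low end.

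It does not follow that true events will be missed in any material number, or that post-discharge severe ARDS escapes capture.

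**What to change.** Close the severe band at PaO2/FiO2 ≤ 100 mmHg. The ARDS component is then one unbroken region, PaO2/FiO2 ≤ 200 mmHg, with the other Berlin criteria kept. That anchor should stay in the text: replacing it with any single reading of 200 or less would redefine the endpoint rather than repair it.

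As a wording alignment only, let the telephone sentence refer to readmission with moderate or more severe ARDS.

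The cost is one inequality sign, a few words, and a check that the endpoint derivation matches. The sample size and the planned analyses are unaffected.

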### Study design

Effect of EARLY administration of DEXamethasone in patients with COVID-19 pneumonia without acute hypoxemic respiratory failure and risk of development of acute respiratory distress syndrome (EARLY-DEX COVID-19) study is a multicenter, randomized, controlled, open-label, parallel-group trial involving 252 hospitalized patients with COVID-19 pneumonia who do not require supplemental oxygen on admission, and laboratory biomarkers related to severe COVID-19 disease are detected. Patients will be randomized and enrolled in Spain. Study sites are listed in the Appendix.

The trial was designed in accordance with the Declaration of Helsinki [22], the Convention of the European Council related to human rights and biomedicine, and within the requirements established by Spanish legislation in the field of biomedical research, the protection of personal data, and bioethics, which was registered on 8 April 2021 at http://www.clinicaltrials.gov with identification no. NCT04836780. The study protocol (version 1.2, 17 April 2021) was approved by the Ethics Committee for investigation with medicinal products of the Comunidad de Madrid, Spain, and the institutional review boards of all participating hospitals (Additional file 1). The trial was approved by the Spanish Agency of Drugs and Medical Devices as a clinical randomized study with drugs on 25 May 2021 (Additional file 2 in Spanish).

Prior to any activity carried out as part of the research, subjects will receive a concise and focused presentation of key information about the clinical trial, verbally and with a written consent form. To be included, written informed consent will be requested from patients’ relatives or legal representative by the local investigators. Following the recommendations of the Spanish Agency of Medicines and Medical Devices, during the COVID-19 pandemic, patient consent can be obtained orally and preferably before an impartial witness, documenting it in the patient’s medical records [23]. The forms have been reviewed by the Ethics Committee that authorized the trial.

Our protocol followed the SPIRIT (Standard Protocol Items: Recommendations for Interventional Trials) guidelines [24]. See Additional file 3 for the SPIRIT checklist of the study protocol.

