### Data collection and procedures study

All participating patients, regardless of the study arm into which they are randomized, will be monitored following general standard of care practices. Patients will be assessed once daily by local investigators.

Demographic data including age and sex assigned at birth, comorbidities, and the COVID-19 vaccination status from participants will be collected. Temperature, respiratory rate, cardiac frequency, peripheral capillary oxygen saturation (SpO2), respiratory support, partial pressure of arterial oxygen/fraction of inspired oxygen (PaO2/FiO2), quick Sequential Organs Failure Assessment (qSOFA) score, and the ordinal scale for clinical improvement of the World Health Organization will be monitored at least once daily. Biochemistry and haematological tests on days 1 and 7; and chest X-ray on days 1, 4, and 7; and discharge will be assessed (Table 2). Laboratory determinations will include haemoglobin, white blood cell, lymphocyte count, platelets count, glucose, blood urea nitrogen, serum creatinine, sodium, potassium, LDH, alkaline phosphatase, albumin, ALT, AST, total bilirubin, CRP, prothrombin time, D-dimer, ferritin level, interleukin-6, and procalcitonin. Patients will be followed up to 90 days after randomization.

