### Secondary outcomes

Secondary outcomes are:Requirement of non-invasive ventilation or invasive mechanical ventilationHospital length of stayAll-cause mortality during the 90-day period following enrolmentAll-cause readmission during the 90-day period following discharge

Local investigators will contact the patient or relatives by phone to ensure the status of the patient on day 90 after randomization. The lead investigator in each site will confirm the recorded 90-day readmission.

The incidence of adverse events and serious adverse events during the study period will be reported.

Results will be communicated at scientific meetings and submitted for publication in peer-reviewed international journals, regardless of the outcome.

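### Health-record extraction of revisits is stated only to 30 days after discharge, while the readmission outcome runs 90 days from discharge, past the day-90 call and the end of follow-up

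*Protocol article*

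**What the plan says.** Four statements in the protocol article bear on how readmissions are found.

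- The Primary outcome section sets the record search: "Electronic health record data related to any inpatient or emergency department revisits within 30 days after discharge will be extracted". Just before that, about the follow-up calls, it says: "Before placing a call, the patient medical record will be reviewed".
- The Secondary outcomes section lists readmission for any cause, counted over 90 days from discharge.
- The same section gives the ascertainment at the end of the study: "Local investigators will contact the patient or relatives by phone to ensure the status of the patient on day 90 after randomization". It adds: "The lead investigator in each site will confirm the recorded 90-day readmission".
- The Data collection section closes follow-up: "Patients will be followed up to 90 days after randomization".

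The Study design section describes a "multicenter, randomized, controlled, open-label, parallel-group trial involving 252 hospitalized patients". Under Randomization, local investigators are the only people who use the allocation system, and under Secondary outcomes local investigators make the day-90 call.

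**The concern.** Readmission is the only listed outcome counted from discharge. The only record search described is also counted from discharge, but it stops a third of the way through the outcome's window. A record search finds an event whether or not the patient mentions it. A telephone call depends on recall and on how the caller asks. If later readmissions are found mainly by telephone, early and late events are captured with different completeness.

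The site lead's confirmation does not clearly close this gap. Read literally, checking a readmission already on record can remove a false report but does not look for one that nobody reported.

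Incomplete capture that is equal in both arms costs events and precision. Unequal capture distorts the comparison, and here patients and callers can know the allocation. The Discussion names the lack of blinding as the main limitation and answers it by pointing to how clear the primary endpoint is. That answer does not extend to readmissions reported by telephone. The outcome also has some weight for safety, because the Safety assessment section records adverse events only until hospital discharge.

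**Working it through.** The plan states no readmission rate, power or precision for this outcome, so there is no figure of its own to reproduce. The check compares time windows.

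**Inputs from the article.** Record extraction: 30 days from discharge. Readmission outcome: 90 days from discharge. Final call and end of follow-up: day 90 from randomisation. Primary outcome: 30 days from enrolment.

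**Assumed input.** L is the number of days from randomisation to discharge. The article gives no value, so L is varied from 3 to 30.

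**Step 1: share of the readmission window outside the extraction.** (90 − 30)/90 = 60/90 = 66.7%.

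**Step 2: how those 60 days divide.** Counted from discharge, the call falls on day 90 − L. The stretch between the end of extraction and the call is (90 − L) − 30 = 60 − L days. The stretch after the call, which is also after follow-up ends, is L days.

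| L (assumed) | Call, days after discharge | After extraction, before call: (60 − L)/90 | After call and follow-up: L/90 |
|---|---|---|---|
| 3 | 87 | 57/90 = 63% | 3/90 = 3% |
| 5 | 85 | 55/90 = 61% | 5/90 = 6% |
| 7 | 83 | 53/90 = 59% | 7/90 = 8% |
| 14 | 76 | 46/90 = 51% | 14/90 = 16% |
| 15 | 75 | 45/90 = 50% | 15/90 = 17% |
| 30 | 60 | 30/90 = 33% | 30/90 = 33% |

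The two shares always add up to 60/90. The final call therefore cannot cover all of the last two thirds for anyone discharged after the day of randomisation.

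**Step 3: what incomplete telephone capture could do (illustration only).** Let f be the share of readmissions that depend on the call, and s the proportion of those that the call finds. The missed share of all readmissions is f × (1 − s). With f from 0.30 to 0.67 and s from 0.90 to 0.70, this runs from 0.30 × 0.10 = 3% to 0.67 × 0.30 = 20%.

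Take equal true risk and the same f in both arms, with s = 0.90 in one arm and 0.70 in the other. The observed risk ratio is (1 − 0.3f)/(1 − 0.1f): 0.91/0.97 = 0.94 at f = 0.30 and 0.799/0.933 = 0.86 at f = 0.67. With the same s and f in both arms the ratio stays at 1. None of the values of f and s comes from the documents.

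**Step 4: is the primary outcome affected?** It reads: "The primary outcome is a composite of development of moderate or more severe ARDS and all-cause mortality during the 30-day period following enrolment". Patients are in hospital when randomised, so discharge cannot come before randomisation. Taking enrolment and randomisation as the same day, discharge plus 30 days falls on day 30 + L, which is never earlier than day 30. The extraction covers the primary window in full.

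**The case against.** The strongest reply is that the extraction sentence stands under the primary outcome and is never named as the source for 90-day readmission. A 30-day extraction for one outcome and a 90-day window for another do not contradict each other. The article is condensed: it cites a full protocol that is not shown, and its schedule table could not be read. The sources for a secondary outcome may be set out there. The record review before calls is worded generally and may already cover the day-90 call. The recorded readmission that the site lead confirms could be one found in the medical record.

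Much of this stands, and it rules out several stronger readings.

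- A reader might infer that two thirds of the window rests on a single unblinded telephone report. Two thirds is the share outside the stated extraction. The part between extraction and call is 50% to 61% of the window for stays of 15 down to 5 days. The site lead's confirmation, and possibly a record review, come on top of the call.
- A reader might infer that late readmissions are in fact under-counted, or that the arm comparison is biased. The article shows only that either could happen.
- A reader might infer that the extraction limit is wrong for the primary endpoint because it runs from discharge. Step 4 shows that this is harmless: the extraction reaches further than needed.

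The reply does not remove the mismatch on the page. The article itself gives the extraction a limit and a time origin, the outcome a longer limit from the same origin, and the call and follow-up another origin. Those dates do not fit together, whatever detail was left to the full protocol.

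**Conclusion.** The point holds as a mismatch between a secondary outcome and its stated ascertainment. Of the 90 days from discharge, 60 (67%) lie beyond the stated record extraction. The end of the window also lies beyond the call and beyond follow-up, by as many days as the patient stayed in hospital after randomisation: 3% to 33% of the window for an assumed 3 to 30 days. The 67% follows from the article alone; the split of it depends on the assumed stay.

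The consequence is a risk that later readmissions are missed and, with an open label, that reporting differs between arms. Its size cannot be computed from the documents. The 3% to 20% missed and the risk ratios of 0.94 to 0.86 show what the assumed inputs would produce and are not estimates for this trial. The primary outcome is not touched. The change is still worth making, because it is cheap and replaces a recall-dependent source with a search that works the same way in both arms.

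**What to change.** 1. Use one time origin for the readmission outcome and its ascertainment. Either count readmissions to day 90 after randomisation, which matches follow-up as planned, or keep 90 days from discharge and extend the final call and follow-up to match. Under the first option, a longer index stay leaves less time in which a readmission can occur. The second gives every discharged patient the same nominal window, at the price of longer follow-up. Extending the extraction to day 90 after randomisation while still counting the outcome from discharge would leave the end of the window uncovered.
2. In the Primary outcome or Secondary outcomes section, state that inpatient and emergency revisits will be extracted from the health record over that whole window, in the same way in both arms.
3. State that the record review before calls also applies to the final call, and that the call supplements the record for admissions to other hospitals.

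The cost is some edited sentences and one further record search per patient, at most 252, by site investigators already in place. The second option in item 1 adds some days of follow-up. No extra patients are needed.

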### Secondary outcomes

Secondary outcomes are:Requirement of non-invasive ventilation or invasive mechanical ventilationHospital length of stayAll-cause mortality during the 90-day period following enrolmentAll-cause readmission during the 90-day period following discharge

Local investigators will contact the patient or relatives by phone to ensure the status of the patient on day 90 after randomization. The lead investigator in each site will confirm the recorded 90-day readmission.

The incidence of adverse events and serious adverse events during the study period will be reported.

Results will be communicated at scientific meetings and submitted for publication in peer-reviewed international journals, regardless of the outcome.

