### Inclusion criteria

To be eligible for inclusion, patients must fulfil the following criteria during screening and prior to enrolment: hospitalized patients aged 18 years or older with confirmed SARS-CoV-2 pneumonia who do not require supplemental oxygen, and risk of developing ARDS. The risk of ARDS is defined by the presence of at least two of the following inflammatory biomarkers: LDH > 245 U/L, CRP > 100 mg/L, and lymphocyte count < 0.80 × 10^9^/L (Table 1).

**Table 1 Tab1:** Inclusion criteria

a) Adults (age 18 years or older)
b) Confirmed COVID-19 based on a positive RT-PCR test or rapid antigen test for SARS-CoV-2 RNA in a respiratory specimen (nasopharyngeal or nasal swab)
c) Requiring in-hospital care
d) A chest imaging study compatible with pneumonia (X-ray or computed tomography)
e) SpO2 ≥ 94% and < 22 bpm breathing on room air
f) The presence of at least two of the following inflammatory biomarkers:
• LDH > 245 U/L
• CRP > 100 mg/L
• Lymphocyte count < 0.80 × 10^9^/L

*Abbreviations: SpO2* Peripheral capillary oxygen saturation, *bpm* Breaths per minute, *LDH* Lactate dehydrogenase, *CRP* C-reactive protein

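### The readmission outcome runs for 90 days from discharge, but stated follow-up stops 90 days from randomisation, so the end of each window has no stated data collection

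*Protocol article*

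**What the plan says.** Five statements in the Protocol article bear on this.

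- **Definition (Secondary outcomes).** All-cause "readmission during the 90-day period following discharge". The clock starts at discharge.
- **End of follow-up (Data collection and procedures study).** "Patients will be followed up to 90 days after randomization". The clock starts at randomisation.
- **Last described contact (Secondary outcomes).** "Local investigators will contact the patient or relatives by phone to ensure the status of the patient on day 90 after randomization".
- **Confirmation (Secondary outcomes).** "The lead investigator in each site will confirm the recorded 90-day readmission". Neither the date of this step nor the day from which the 90 days are counted is given.
- **Record extraction (Primary outcome).** "Electronic health record data related to any inpatient or emergency department revisits within 30 days after discharge will be extracted". This is the only data collection counted from discharge, and it covers 30 days.

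Participants are inpatients at entry: Table 1 of the inclusion criteria has "c) Requiring in-hospital care". Discharge therefore normally falls after randomisation. The neighbouring outcome of 90-day mortality is counted from enrolment, so it fits the follow-up horizon. Readmission does not.

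**The concern.** A window that opens at discharge closes at discharge plus 90 days, which is later than day 90 after randomisation for anyone who stays in hospital after being randomised. A readmission can therefore count under the definition and still fall after stated follow-up has ended. For example, a patient discharged on day 10 and readmitted on day 95 is at day 85 after discharge: inside the outcome window, outside follow-up.

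Two things are at stake. First, sites could apply different windows, since the confirmation step does not say which 90 days it means. Second, the uncovered time grows with length of stay, which is itself a secondary outcome and could differ between arms. The arm with longer stays would then have less time in which a readmission could be recorded, and would tend to show fewer of them.

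**Working it through.** The article states no figure for this outcome that could be reproduced, so the check is arithmetic on the two windows.

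**Inputs**

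- Window required: 90 days from discharge (Secondary outcomes).
- Follow-up stated: 90 days from randomisation (Data collection and procedures study; Secondary outcomes).
- Extraction counted from discharge: 30 days (Primary outcome).
- L, days from randomisation to live discharge: not given. The values below are assumptions.

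**Step 1: uncovered part of the window.** The window ends on day 90 + L after randomisation and stated follow-up ends on day 90. Covered time is 90 − L days, uncovered time is L days, and the uncovered share is L/90.

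| Assumed L (days) | Covered (days) | Uncovered share |
|---|---|---|
| 3 | 87 | 3.3% |
| 7 | 83 | 7.8% |
| 10 | 80 | 11.1% |
| 14 | 76 | 15.6% |
| 20 | 70 | 22.2% |
| 30 | 60 | 33.3% |

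**Step 2: does the 30-day extraction fill the gap?** It ends on day L + 30 after randomisation. It passes day 90 only if L exceeds 60, and even then it stops 60 days short of the end of the window (90 − 30 = 60). For every stay in the table it adds nothing beyond day 90.

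**Step 3: effect on a comparison of arms.** What matters here is the difference in stay. Assume a constant readmission hazard, the same true 90-day risk r in both arms, and one length of stay per arm. Then

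observed risk = 1 − (1 − r)^((90 − L)/90).

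For r = 10% and L = 7: 1 − 0.90^(83/90) = 9.26%. For L = 10: 1 − 0.90^(80/90) = 8.94%.

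| Assumed r | L = 7 | L = 10 | L = 14 | L = 30 |
|---|---|---|---|---|
| 5% | 4.62% | 4.46% | 4.24% | 3.36% |
| 10% | 9.26% | 8.94% | 8.51% | 6.78% |
| 20% | 18.60% | 17.99% | 17.17% | 13.82% |

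At r = 10%, the spurious difference between arms is:

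- 7 against 10 days: 9.26 − 8.94 = 0.32 points, or 0.0032 × 126 = 0.4 of a patient in an arm of 126;
- 7 against 14 days: 9.26 − 8.51 = 0.75 points, or 0.9 of a patient;
- 7 against 30 days: 9.26 − 6.78 = 2.48 points, or 3.1 patients.

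The patient counts treat all 126 as discharged alive, so they are upper values.

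**The case against.** **The window might still be observed.** A reader might infer that the outcome cannot be fully observed. The text does not go that far. The site lead's confirmation has no date, the trial uses medical record review elsewhere, and the schedule in Table 2 is not reproduced in the text available. A later record check is not excluded. This stands as a limit on the wording: the gap is in what is stated. It does not remove the conflict, because the article puts the end of follow-up at day 90 after randomisation and describes no later step.

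**The comparison might not be between randomised groups.** A reader might also infer that the analysis is restricted to patients discharged alive, and that an arm that saves frail patients would therefore look worse on readmission. The definition suggests such a denominator, but the article states none for this outcome. The analysis set and the handling of death can properly be left to an analysis plan that is not shown, and the article gives no mortality or readmission rates with which to argue the second step. Neither is held against the plan.

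**The distortion is small.** This is largely right. The stays are assumed, the lost time is the end of the window, and a modest difference in stay moves the observed risk by a fraction of a percentage point. Larger effects need large differences in stay.

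**Moving the origin does not equalise time at risk.** This is also right. A patient cannot be readmitted before discharge, so 90 − L days at risk remain even when the outcome is counted to day 90 after randomisation. Treating death as a competing event does not change that. What the move secures is an outcome that stated follow-up covers completely and that is defined for every randomised patient.

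**Conclusion.** The point holds as an inconsistency between two stated rules, not as missing detail: the readmission window and the follow-up period have different origins, and no stated procedure covers the difference. The uncovered part equals the stay after randomisation (for stays up to 60 days), which is 8%, 22% and 33% of the window at assumed stays of 7, 20 and 30 days.

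Between arms, the effect depends on the difference in stay: about 0.3 percentage points for 7 against 10 days and about 2.5 for 7 against 30 days, given an assumed 10% risk, constant hazard and no collection after day 90. The documents do not support a claim of serious bias.

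This is a secondary outcome. The sample size rests on ARDS, and the primary result is unaffected. The definition should be corrected before analysis.

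**What to change.** Use one time origin for the outcome and for follow-up.

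**Preferred.** Define the outcome as any all-cause readmission up to day 90 after randomisation, in all randomised patients, with death as a competing event. The existing day-90 call covers this in full, and the window then lines up with 90-day mortality. State that time at risk after discharge still depends on length of stay, so the result is to be read alongside length of stay and 90-day mortality. If a single summary is wanted, days alive and out of hospital to day 90 takes stay, readmission and death together.

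**Alternative.** Keep the discharge-based definition and extend the record check or call to 90 days after discharge, that is, to day 90 + L after randomisation. The uncovered time is then zero for every stay.

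Under either option, the confirmation step should say when it takes place and which 90 days it covers.

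**Cost.** A small amendment to the definition and analysis of one secondary outcome, in a trial that is registered and recruiting, so the registration should be updated as well. The preferred option needs no added follow-up; the alternative needs one later check per discharged patient.
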